### Inclusion criteria

Meet the American College of Rheumatology (ACR) criteria for symptomatic knee OA [24], assessed by a rheumatologist;Age 50 to 75 years;Body mass index (BMI) ≥ 24 kg/m^2^;Knee pain ≥20 on a 100 mm VAS;Being able to listen, speak, read and understand Chinese, capable of understanding the study requirements and willing to cooperate with the study instructions, and able to provide written informed consent.

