### Exclusion criteria

Severe radiographic knee OA as grade 3 joint space narrowing according to the Osteoarthritis Research Society International (OARSI) atlas [25];Severe knee pain as knee pain ≥80 on a 100 mm VAS;Planned knee or hip surgery (including arthroscopy, joint replacement, and joint open operation) within 2 years;Severe knee trauma history (including arthroscopy, severe injury of knee ligament or meniscus);Contraindication to magnetic resonance imaging (MRI) scanning (e.g., implanted pacemaker, artificial metal valve or cornea, aneurysm clipping surgery, arterial dissection, metal foreign bodies in the eyeball, claustrophobia);Other forms of inflammatory arthritis (e.g., rheumatoid arthritis, psoriatic arthritis);Active malignant cancer or other life-threatening diseases;Type 1 or type 2 diabetes mellitus;Clinical manifestation of liver dysfunction or elevated alanine aminotransferase/aspartate aminotransferase levels exceeding 2 times the upper limit of normal values;Estimated glomerular filtration rate of less than 60 ml/min/1.73 m^2^;Hypoxic state (e.g., chronic heart insufficiency, acute myocardial infarction, heart failure, chronic obstructive pulmonary disease, cor pulmonale, peripheral vascular disease);Alcoholism;Pregnancy or lactation;Allergic to metformin hydrochloride;Conditions affecting the absorption of oral drugs (e.g., postgastrectomy and malabsorption syndrome);Use of metformin in recent 30 days or plan to use metformin in the next 2 years;Use of investigational drug in recent 30 days.

Note: when both knees of the participants meet the eligibility criteria, the knee with more severe VAS pain will be selected as the study knee.

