### Outcome measures

Primary outcomes will be changes in tibiofemoral cartilage volume and WOMAC score over 24 months. Secondary outcomes will be changes in VAS knee pain, tibiofemoral cartilage defects, effusion-synovitis volume, and tibiofemoral bone marrow lesions maximum size over 24 months.

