#### Assessment of knee symptoms

Knee symptoms will be assessed by WOMAC score and VAS knee pain at baseline and 3-month, 6-month, 12-month, and 24-month follow-up (Table 1).

The WOMAC system in a 100-mm visual analog format will be used to quantify the degree of knee pain (5 questions), joint stiffness (2 questions), and physical dysfunction (17 questions) during the last 7 days [26]. The WOMAC score will be calculated by summing the score of each question (1 point for every 1 mm), and a higher score of WOMAC represents a more severe OA symptom. The WOMAC score will be considered invalid and treated as missing data if more than 5 of the questions are not answered. In case no more than 5 items are missed, the remaining items will be averaged and then multiplied by 24 to create the WOMAC score.

The 100 mm VAS will be used to assess the knee pain during the last 7 days, and a higher VAS indicates a more severe knee pain.

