### Statistical analysis plan

Baseline characteristics will be reported per group using descriptive statistics (means, proportions, and medians as appropriate) without statistical tests.

The primary analyses will be intention-to-treat analyses of primary and secondary outcomes. Per-protocol analyses will be performed as the secondary analyses, and participants with an average daily dose of 0.5-2 g of the investigational drug will be included in the per-protocol analyses. Missing data caused by loss to follow-up and nonresponses will be addressed by multiple imputations with chained equations. Imputations will be performed separately for each treatment group and each outcome using baseline variables of age, sex, BMI, and study site and non-missing values of the outcomes at baseline and each follow-up with the assumption of data missing at random. The treatment effect will be analyzed using linear mixed effect models. In the models, baseline covariates (age, sex, BMI, baseline value of the corresponding outcome), treatment, month, and the interactions of covariates and treatment with month will be entered as fixed effects. The correlation within the study sites and the repeated measures will be addressed using trial site and participant identification as random intercepts. Month will be treated as random slope to allow different treatment effects among knee OA patients over time. Changes in outcome measures within each group and difference of the changes between groups from baseline to follow-up will be calculated using linear combinations of the estimated coefficients.

Pre-specified stratified analyses will be performed to explore whether BMI could affect the treatment effect of metformin on knee OA. This will be conducted by introducing a 3-way interaction between treatment, month, and BMI in the linear mixed-effects models.

Because of the potential for type I error due to multiple comparisons, the findings for the analyses of the secondary outcomes and the stratified analyses will be interpreted as exploratory. A 2-sided *P* value of 0.05 or less will be considered as statistically significant.

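### VAS knee pain is recorded at screening and at month 0, but its model adjusts for one baseline value, so a free covariate for this secondary outcome goes unused

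*Protocol article*

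**What the plan says.** In Table 1 of the protocol article, the knee pain VAS row is ticked at screening, month 0 and months 3, 6, 12 and 24. The WOMAC row is ticked from month 0 onwards, with no screening reading. The text counts one baseline for both: "Knee symptoms will be assessed by WOMAC score and VAS knee pain at baseline and 3-month, 6-month, 12-month, and 24-month follow-up" (Assessment of knee symptoms).

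The Statistical analysis plan section specifies linear mixed models with "In the models, baseline covariates (age, sex, BMI, baseline value of the corresponding outcome" among the fixed effects, each with a month interaction. The imputation models likewise draw on outcome values at baseline and each follow-up. Neither description mentions the screening VAS.

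VAS knee pain decides who enters. The lower limit is "Knee pain ≥20 on a 100 mm VAS" (Inclusion criteria) and the upper limit is set by excluding "Severe knee pain as knee pain ≥80 on a 100 mm VAS" (Exclusion criteria). If both knees qualify, "the knee with more severe VAS pain will be selected as the study knee".

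VAS knee pain is a secondary outcome (Outcome measures), and "the findings for the analyses of the secondary outcomes and the stratified analyses will be interpreted as exploratory" (Statistical analysis plan).

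**The concern.** One seven-day recall of pain on a 100 mm scale is a noisy measure of a person's usual pain. A second reading taken before treatment carries some information on that level that the month-0 reading lacks. The trial collects the second reading anyway, and the listed covariates make no use of it. The residual variance in the VAS knee pain comparison is then somewhat larger than the data require.

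Only precision on one exploratory outcome is at stake. There is no risk of bias, because adjusting or not adjusting for a pre-randomisation variable leaves the treatment contrast valid either way.

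**Working it through.** **The plan's own figures.** The formula is n = 2 × [(1.96 + 0.842) × σ/δ]².
- Cartilage volume, σ = 1.92 and δ = 1.07: n = 50.56; the article states 51.
- WOMAC, σ = 413.74 and δ = 0.16 × 99.95 × 10 = 159.92: n = 105.10; the article states 105.
- Dropout: 105 / 0.8 = 131.25; the article states 131.

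These agree with the article to within rounding. None of them involves VAS or the number of baseline readings.

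**Inputs for VAS.** The article gives no standard deviation or correlation for VAS, so these are assumed:
- r, the correlation of each pre-treatment reading with month 24: 0.3 to 0.6.
- ρ, the correlation of screening with month 0: 0.4 to 0.9, with r no larger than ρ.

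**Formulas.** Take readings of equal variance and the month-24 value as the outcome. The unexplained share of its variance is
- with month 0 only: 1 − r²
- with screening and month 0: 1 − 2r²/(1 + ρ)

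**Before allowing for eligibility:**

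| ρ | r | one reading | two readings | fall in variance |
|---|---|---|---|---|
| 0.4 | 0.4 | 0.840 | 0.771 | 8.2% |
| 0.5 | 0.5 | 0.750 | 0.667 | 11.1% |
| 0.6 | 0.6 | 0.640 | 0.550 | 14.1% |
| 0.7 | 0.4 | 0.840 | 0.812 | 3.4% |
| 0.8 | 0.4 | 0.840 | 0.822 | 2.1% |
| 0.9 | 0.3 | 0.910 | 0.905 | 0.5% |

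The first three rows suppose that two pre-treatment readings agree no better than readings 24 months apart. That is favourable to the gain. Where ρ exceeds r, which is more usual, the gain shrinks. At ρ = 0.7 and r = 0.4 the standard error falls by 1.7%, and a comparison with 80% power would rise to 81.3%.

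**After allowing for eligibility.** Simulated screening readings were restricted to 20 to below 80 mm, with an assumed mean of 40 to 50 mm and standard deviation of 20 to 25 mm before restriction. The correlations in this table are also those before restriction.

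| ρ | r | fall in variance |
|---|---|---|
| 0.4 | 0.4 | about 4% to 5% |
| 0.5 | 0.5 | about 5% to 7% |
| 0.6 | 0.6 | about 7% to 10% |
| 0.7 | 0.4 | about 2% |
| 0.8 | 0.4 | about 1.3% to 1.6% |
| 0.8 | 0.3 | about 0.7% to 0.9% |

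The restriction removes roughly a quarter to a half of the gain in most of these cases. The gain stays positive in all of them.

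**The case against.** The strongest reply is that nothing here is wrong. Adjusting for one baseline value of the outcome is standard and unbiased, the article is consistent in counting one baseline symptom assessment, and a fuller analysis plan could say more about the screening reading. This stands in so far as the point is an improvement and not the correction of an error. However, the article does state its covariate list, and that list can be judged against the data it schedules.

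A second reply is that the screening reading is not a clean replicate. It evidently serves eligibility and the choice of study knee, so it is range-restricted and open to regression to the mean. This is a good reason not to average it into the baseline from which change is measured, and it reduces the gain. It does not make the reading invalid as a covariate, because selection on it happens before randomisation and affects both arms alike.

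A third reply is that the variance formulas describe a single-visit analysis of covariance, whereas the plan is a repeated-measures mixed model with multiple imputation. That stands too: the percentages are a guide to size and not a forecast for the planned model.

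A reader might also infer that all the symptom comparisons, including the WOMAC co-primary, lose a second baseline reading. Table 1 does not support this, since WOMAC is not measured at screening. Putting VAS into the WOMAC model would be a separate proposal about a different instrument, and its benefit would depend on a set of correlations the article does not supply. A reader might likewise take the 8% to 14% in the first three rows of the first table as the expected gain. Those figures need ρ equal to r and ignore the eligibility limits.

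**Conclusion.** The point holds as an optional gain in efficiency for one secondary, exploratory outcome. The stated VAS knee pain model leaves out a valid pre-treatment covariate that Table 1 already schedules. Under assumed correlations, and allowing for the eligibility range, the residual variance would fall by roughly 2% to 10%. About 2% to 3% is a reasonable central expectation if the pre-treatment readings correlate 0.7 and each correlates 0.4 with month 24. The gain drops below 1% if the two readings correlate very highly. All these figures depend on correlations and a VAS distribution that the article does not give. The single-baseline model is unbiased. The WOMAC co-primary analysis and the sample size are not affected.

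**What to change.** Add one sentence to the analysis plan, for the VAS knee pain model only. It should say that the baseline for change is the month-0 VAS, and that the study knee's screening VAS enters as a further covariate with its month interaction. The same variable should go into the imputation model for VAS, so that the two models match.

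The wording should be fixed before the first unblinding step, so that the covariate choice cannot be linked to results. The cost is one or two degrees of freedom among 262 participants, taking month as continuous, with no new data and no extra visit. The WOMAC model and the sample size section need no change.

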### Sample size

The sample size calculations were performed using the formula: n_1_ = n_2_ = 2 × [(Z_α_ + Z_β_) × σ/δ]^2^ and assumed α = 0.025 (one-sided) and β = 0.20 (Z_α_ = 1.96; Z_β_ = 0.842).

According to a previous study, the standard deviation of annual tibiofemoral cartilage volume loss in obese knee OA patients was 1.92% (σ), and taking metformin could decrease the average annual tibiofemoral cartilage volume loss by 1.07% (δ) [22]. Considering that it may take a long time for metformin to exert the protective effect on articular cartilage, we assumed that the volume of articular cartilage begins to differ after 1 year of metformin use, that is, the second year of follow-up can be used to observe the effect of metformin on the articular cartilage volume. Based on the assumption and the data from the previous study, we calculated that 51 participants per group (n_1_, n_2_) are needed.

Sample size calculation was also performed based on another primary outcome, namely, WOMAC score. Up to now, no study has reported the effect of metformin on WOMAC score. We hypothesized that metformin treatment for 2 years will have more decrease in WOMAC score compared with placebo. The minimum clinically important difference (MCID) of WOMAC score in patients with knee OA was reported being 12, 14, 16, 18, and 20% of the baseline score [29–33]. Combined, we took the 16% for sample size calculation. In our previously established Chinese symptomatic knee OA cohort, the mean baseline WOMAC score was 99.95 (a total score of 240) [28]. Based on these data, it is estimated that the difference in the changes in WOMAC score (a total score of 2400) between metformin and placebo groups needs to be greater than 159.92 (δ) to achieve MCID. In our previous clinical trials for patients with knee OA, the standard deviation of change from baseline to two-years follow-up of WOMAC score was 413.74 (σ). Therefore, the sample size was calculated as 105 for each group (n_1_, n_2_).

Take into consideration of these two calculations and a 20% dropout over the trial, 131 participants in each arm will be sufficient to detect the differences of primary outcomes between the two groups.

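### As most naturally read, the analysis model fits the WOMAC treatment effect as a straight line from 0 to 24 months, so the 24-month difference is estimated without bias only for some time courses

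*Protocol article*

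**What the plan says.** The Statistical analysis plan section of the protocol article specifies one linear mixed model for the outcomes. Besides age, sex, BMI and the baseline value of the outcome, "treatment, month, and the interactions of covariates and treatment with month will be entered as fixed effects". Site and participant are random intercepts, and "Month will be treated as random slope to allow different treatment effects among knee OA patients over time". The reported result is the within-group change and the between-group "difference of the changes between groups from baseline to follow-up will be calculated using linear combinations of the estimated coefficients".

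The section does not say whether month is numeric or categorical in the fixed part, nor whether the month-0 value is an outcome row as well as a covariate.

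Under Assessment of knee symptoms, "Knee symptoms will be assessed by WOMAC score and VAS knee pain at baseline and 3-month, 6-month, 12-month, and 24-month follow-up". MRI outcomes are scheduled at 0 and 24 months only (Table 1). Under Outcome measures, "Primary outcomes will be changes in tibiofemoral cartilage volume and WOMAC score over 24 months". The Sample size section "assumed α = 0.025 (one-sided) and β = 0.20", and states that the WOMAC difference in changes "between metformin and placebo groups needs to be greater than 159.92 (δ) to achieve MCID". The standard deviation it uses, 413.74, is for the change from baseline to two years.

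**The concern.** The endpoint and the sample size both concern the difference at 24 months. If month is numeric, the model estimates something else: a single rate of divergence between the arms, multiplied by 24. The two agree when the effect grows in proportion to time and otherwise only by coincidence of shape. Visits at 3, 6 and 12 months, collected to describe the course, then help determine the 24-month estimate, and an early effect counts against it.

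The document offers no basis for a WOMAC effect that grows linearly. The Sample size section says that no study has yet reported how metformin affects WOMAC. At stake are the size of the estimate and the power for one of the two primary outcomes.

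**Working it through.** **Plan's own figure.** δ = 0.16 × 99.95 × (2400/240) = 159.92. n = 2 × [(1.96 + 0.842) × 413.74/159.92]² = 105.1, given as 105 per group. 105/0.8 = 131.25, given as 131. The plan's figures are reproduced. They rest on a simple comparison of 24-month change.

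**Reading used.** (a) Month is numeric, because a random slope needs a numeric scale and no visit factor is named. (b) Month 0 is an outcome row. The same model is applied to cartilage volume, which has only months 0 and 24, so the month terms cannot be estimated without that row. (c) The contrast is the difference in change from baseline, so the treatment main effect cancels and 24 × the treatment-by-month coefficient remains.

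**Weights.** Visits t = 0, 3, 6, 12, 24 have mean 9, and Sxx = 81 + 36 + 9 + 9 + 225 = 360. With all visits present and a random intercept and slope, generalised and ordinary least squares give the same slope. The contrast is therefore 24 × Σ(t − 9)y/360 = Σ(t − 9)y/15, where y is the true treatment difference at each visit. With no difference at baseline:

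24 × slope = y24 + 0.2·y12 − 0.2·y6 − 0.4·y3

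**Result by shape** (effect at 3, 6, 12 and 24 months as a share of the 24-month effect; the shapes are assumptions):

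| Course | Shares | Estimate / truth |
|---|---|---|
| Complete by month 3 | 1, 1, 1, 1 | 1 + 0.2 − 0.2 − 0.4 = 60% |
| Three quarters at 3, full at 6 | 0.75, 1, 1, 1 | 70% |
| Half at 3, full at 6 | 0.5, 1, 1, 1 | 80% |
| Exponential, time constant 1.5 months | 0.865, 0.982, 1.000, 1 | 66% |
| Exponential, time constant 3 months | 0.632, 0.865, 0.982, 1 | 77% |
| Exponential, time constant 6 months | 0.401, 0.644, 0.881, 1 | 89% |
| Linear rise to 12, then flat | 0.25, 0.5, 1, 1 | 100% |
| Nothing at 3, full from 6 | 0, 1, 1, 1 | 100% |
| Linear throughout | 0.125, 0.25, 0.5, 1 | 100% |
| Nothing before 12, full from 12 | 0, 0, 1, 1 | 120% |

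For the first row, Sxy = −6 − 3 + 3 + 15 = 9, the slope is 9/360 = 0.025, and 24 × 0.025 = 0.60. The fitted effect at month 0 is 0.8 − 9 × 0.025 = 0.575, which is the part absorbed by the treatment main effect. On the WOMAC scale, 0.60 × 159.92 = 95.95.

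**Power for that row.** With SD 413.74 and 105 per group, SE = 413.74 × √(2/105) = 57.1. Then z = 95.95/57.1 = 1.68 and power = Φ(1.68 − 1.96) = 39%. A slope-based contrast can have a smaller SD. If a share f of the change variance comes from the random slope, its SD is 413.74 × √(0.8 + 0.2f): 370 at f = 0 and 403 at f = 0.75 (f is an assumption). Power is then 47% and 41%. The plan's figure is 80%.

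**Rough check.** A small mixed-model simulation of the first row (15 runs, 200 per arm, assumed variance components) gave 54% for 24 × slope (SE 4 points) and 90% for categorical month (SE 5 points). These agree with 60% and 100% within about two standard errors. The algebra carries the point, not the simulation.

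**The case against.** The strongest reply is that the text never says linear. A categorical fixed month with a numeric random slope is a possible model, linear combinations of coefficients fit either coding, and an article may leave time coding to a fuller plan. This stands against any claim that the plan forces a straight line. It does not remove the point: the section does state a model, and its natural reading is numeric month.

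Second, other readings of the same sentences change the number. For an effect complete by month 3, adding the main effect back gives 0.575 + 0.60 = 117.5%, but that is a difference in level, not in change from baseline. Using follow-up rows only, with main effect plus 24 × slope, gives 100% for that shape. That reading fits poorly with the cartilage outcome, and over the other shapes in the table it gives 100% to 117%, so it is not generally unbiased either.

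Third, a reader might infer that any early effect that plateaus is cut to 60%. The table shows otherwise: that figure belongs to an effect complete by month 3, and some plateaus are estimated correctly or overestimated. The titration schedule does not settle the shape, since reaching a dose is not the same as reaching a full symptom response. A step at month 3 has no more support in the document than a straight line.

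Fourth, a reader might use the delayed cartilage effect assumed in the Sample size section as evidence against the model. It is not: cartilage is measured twice, so linearity cannot constrain it. The same shape at the WOMAC visits (0, 0, 0, 1) would give 100%.

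Finally, if there is no effect at any visit the contrast has no bias. The matter is estimate size and power, not false positives under that null. This stands.

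**Conclusion.** The point holds in conditional form. If month is numeric, month 0 is an outcome row and the contrast is the difference in change from baseline, the WOMAC estimate at 24 months depends on the shape of the effect. Over the shapes examined it runs from 60% to 120% of the truth. At the low end, power is about 39% to 47% against the planned 80%. These figures assume no baseline difference and complete visits for 105 per group.

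A baseline-adjusted analysis at 24 months might exceed 80% power, but the protocol gives no baseline correlation, so 80% is the only comparator that the document supports. The weakness is more than missing detail, because following the stated model as read can misestimate a primary outcome that is defined and sized at 24 months. It should be changed; it does not invalidate the design.

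**What to change.** For WOMAC, and for VAS knee pain, which has the same follow-up visits:

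- enter visit as a categorical factor (3, 6, 12, 24 months) with a treatment-by-visit interaction;
- adjust for the baseline value and the other listed covariates;
- name the treatment difference at 24 months as the primary contrast.

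An unstructured within-patient covariance is one suitable option in place of the random slope. With complete data, the contrast then recovers the 24-month effect whatever its course. Cartilage volume and the other MRI outcomes need no change on this account.

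The cost is a few sentences in the analysis plan, settled before unblinding, with no change to visits or data. The model has a few more parameters. If the effect is truly linear, some power is given up: with the SDs above, the linear contrast would have about 82% to 88% power for 159.92, against 80% for the simple 24-month comparison.

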## Methods/design

### Study design

This study is designed as a multicenter, randomized, double-blind, placebo-controlled trial over 24 months. Two hundred and sixty-two symptomatic knee OA patients with overweight will be recruited and randomly allocated to either the treatment or placebo control group. The recruitment strategy will include collaborations with specialist rheumatologists, orthopedic surgeons, rehabilitation physicians, and general practitioners, as well as advertising through posters and social media. The primary site of this trial is Guangzhou First People’s Hospital with ethics approval being received from the Ethics Committee of Guangzhou First People’s Hospital (reference number: K-2021-001-02). The sub-sites initially include: Sun Yat-sen Memorial Hospital of the Sun Yat-sen University, Zhujiang Hospital of Southern Medical University, Foshan First People’s Hospital, Liwan Central Hospital of Guangzhou, the Third People’s Hospital of Shenzhen and the Second Affiliated Hospital of Nanchang University. Ethics approval will be received from each of the institutions before the recruitment. Competitive enrollment will be adopted among study sites. Informed written consent will be obtained from all participants. Reporting of the trial will be guided by the Consolidated Standards of Reporting Trials (CONSORT) Statement [23]. The study design of this trial is depicted by Fig. 1.

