### Randomization and blinding

To control for variation in study sites, the randomization will be stratified by the study sites. Participants in each site will be randomly assigned to the intervention arm or placebo arm in a ratio of 1:1 based on computer generated random numbers using block randomization (with a block size of 6). Participants, investigators, outcome assessors, as well as statisticians will be blinded to the group allocation in this trial. Allocation concealment will be ensured by keeping the allocation data confidential and using the visual- and taste-masked inert placebo. Emergency unblinding will be permissible when a serious adverse event happens. Participants who are unblinded will be withdrawn from the trial.

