#### Assessment of knee structures

Knee structural changes will be assessed using MRI at baseline and 24-month follow-up (Table 1). MRI sequences sensitive for cartilage [e.g., 3D dual-echo in steady state (DESS) or 3D Water Selected fluid (WATSf) sequences] will be used to assess tibiofemoral cartilage volume. MRI sequences sensitive for detailed anatomy [e.g., 2D intermediate-weighted fat suppression or 2D proton density-weighted fat suppression sequences] will be used to assess tibiofemoral cartilage defects, effusion-synovitis volume, and tibiofemoral bone marrow lesions maximum size. All these knee structures will be assessed on the sagittal images. Besides, coronal sequences sensitive for detailed anatomy will be also acquired to assist sagittal images positioning. Details of MRI sequences and parameters will be determined according to the magnetic resonance (MR) scanner available at each site. Before the enrollment, the specific MRI sequences and parameters will be tested in corresponding MR scanners to ensure the MR image meets the study requirement.

**Table 1 Tab1:** Schedule of data collection

	Screening	months				
		0	3	6	12	24

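### Site stratifies the randomisation but enters the model only as an intercept, which on the natural reading cancels from the difference in change; adding site-by-month would recover a little precision

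*Protocol article*

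**What the plan says.** The Randomization and blinding section of the protocol article gives the reason for the design: "To control for variation in study sites, the randomization will be stratified by the study sites". It adds that "Participants in each site will be randomly assigned to the intervention arm or placebo arm in a ratio of 1:1", in blocks of six. The Study design section names one primary site and six sub-sites, seven in all. The list is provisional ("The sub-sites initially include") and site sizes will differ ("Competitive enrollment will be adopted among study sites").

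The Statistical analysis plan section takes age, sex, BMI and the baseline value of the outcome as covariates and says that "treatment, month, and the interactions of covariates and treatment with month will be entered as fixed effects". Site is not in that list. Its role is given separately: "The correlation within the study sites and the repeated measures will be addressed using trial site and participant identification as random intercepts". Month also has a random slope, whose stated purpose is to let effects vary across patients; no grouping level is named. The treatment effect is the between-group difference in change from baseline, built from the model coefficients. Site is also used in the imputation model.

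**The concern.** When allocation is balanced within site, site differences in change fall about equally on both arms and largely drop out of the treatment difference. The analysis keeps that benefit only if its error term also excludes them. A site intercept raises or lowers all of a site's visits by the same amount, so it describes differences in level. The quantity tested is a difference in change. If sites differ in change, the listed terms have nowhere to put that variation except the participant slope and the residual. The standard error then describes a less precise comparison than the one the randomisation delivered.

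At stake are slightly wide intervals and a slightly conservative test on both co-primary outcomes. For the MRI outcomes there is a conceivable source of site variation, since "Details of MRI sequences and parameters will be determined according to the magnetic resonance (MR) scanner available at each site". For WOMAC it would be differing placebo response or co-treatment between sites.

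**Working it through.** **Inputs.** From the Sample size section: WOMAC SD of change 413.74, target difference 159.92, 105 completers per arm, 20% dropout; cartilage SD 1.92% and difference 1.07% per year. From Study design: seven sites. The share ρ of the variance of change that lies between sites is not in the documents, so it is an assumption, shown from 0 to 20%.

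**The plan's own figures.** Per arm, n = 2 × [(1.96 + 0.842) × σ/δ]².
- WOMAC: 2 × (2.802 × 413.74/159.92)² = 105.1 (stated 105).
- Cartilage: 2 × (2.802 × 1.92/1.07)² = 50.6 (stated 51).
- Dropout: 105/0.8 = 131.25 (stated 131).

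The sizes reproduce. They use the total SD with no allowance for site, so the planned WOMAC standard error is 413.74 × √(2/105) = 57.1.

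**Does the site intercept act on the contrast?** Write a participant's outcome as fixed effects + site intercept + participant intercept + participant slope × month + error. In the 24-month value minus the baseline value, both intercepts cancel. As a numerical check, a reduced form of the model (treatment, month and their product; participant intercept and slope; visits at 0, 3, 6, 12 and 24 months; seven unequal sites) was fitted by generalised least squares with the site-intercept variance set to 0, 100², 200² and 1000². The treatment-by-month estimate was 0.8417 with standard error 2.3242 every time. The result is exact for complete data, and multiple imputation makes each analysed data set complete.

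**Size, closed form.** Ignoring site in the change, the reported variance is about 2σ²/n. Under site-blocked allocation the true variance is about 2σ²(1 − ρ)/n. The standard error is therefore overstated by the factor 1/√(1 − ρ), and the true two-sided type I error is 2 × [1 − Φ(1.96/√(1 − ρ))].

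| ρ (assumed) | SE overstated by | True type I error | WOMAC power with site-by-month, 105 per arm |
|---|---|---|---|
| 0 | 0% | 5.0% | 80.0% |
| 2% | 1.0% | 4.8% | 80.8% |
| 5% | 2.6% | 4.4% | 82.0% |
| 10% | 5.4% | 3.9% | 83.9% |
| 20% | 11.8% | 2.8% | 87.9% |

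**Size, simulation.** 10,000 trials per setting, 210 analysed, sites of 80, 40, 30, 20, 18, 12 and 10, blocks of six within site, change analysed without and with site:

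| ρ | Mean SE without / with | Power without / with | Type I error without / with |
|---|---|---|---|
| 0 | 57.0 / 57.0 | 79.7% / 79.6% | 4.6% / 4.6% |
| 5% | 56.7 / 55.6 | 80.6% / 81.6% | 4.6% / 4.9% |
| 10% | 56.5 / 54.2 | 81.5% / 83.9% | 4.0% / 4.9% |
| 20% | 55.7 / 51.1 | 83.4% / 87.8% | 3.4% / 5.0% |

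The simulated excess is a little smaller than the closed form (about 2% at ρ = 5%, 4% at 10%). With few, unequal sites the pooled variance picks up only part of ρ. Here the sum of squared site shares is 9,868/44,100 = 0.224, so the ratio at 10% is √[(1 − 0.0224)/0.90] = 1.042, as simulated.

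**The case against.** The strongest reply is that the result depends on two details the article does not fix. If month were also random at site level, site differences in change would be modelled and the point would fall. The section names no level; the stated purpose points to the participant but does not settle it. Second, having the baseline value as a covariate also fits a model with post-baseline responses only, in which the WOMAC site intercept would do part of the work. That escape is not open to cartilage volume: with one follow-up scan, a model with month effects needs baseline as a response. A condensed article may leave such details to a fuller plan. Both conditions stand as limits on the point.

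The MRI argument also has a limit. A stable scanner offset is a difference in level and cancels from change, and all images are to be assessed uniformly after follow-up. Nothing in the documents shows that sites will differ in cartilage change, and no MRI magnitude is computed here.

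The figures above compare raw change, without the age, sex, BMI and baseline terms by month, which may absorb some site variation. A small check with the five-visit mixed model (12 data sets per setting) gave mean standard errors of 54.08 with a site level term and 52.38 with site-by-month at a 10% share, a ratio of 1.03.

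A reader might go further and infer that the trial loses planned power or that its primary tests are invalid. The documents do not support either. The planned standard error is 57.1, and the simulated one without site never exceeds 57.0. Power without site stays at about 80% or above in every setting. The error is conservative, so it cannot create a false positive.

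**Conclusion.** The point holds in a limited form, as a cheap improvement. With baseline as a response row and a participant-level month slope, the only site term in the model has no effect on the difference in change, although site is the factor that allocation was stratified on. The reported standard error is then overstated by about 1 to 3% if 2 to 5% of the variance of change lies between sites, by about 5% at 10%, and not at all at 0%. The share is assumed, and only the part left after the listed covariates counts. There is no bias, and the planned 80% power is met. What is given up is precision that the stratified design already makes available: about 1 power point for WOMAC at a 5% share and about 2 at 10%. Under either alternative reading of the model, the loss shrinks or disappears.

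**What to change.** In the Statistical analysis plan section, add site to the baseline covariates that interact with month, so that site and site-by-month are fixed effects in place of the site random intercept. State a rule for pooling very small sites. If many small sites are added through competitive enrolment, a site-level random month slope would do similar work and stay closer to the present wording. For the MRI outcomes, include site as a fixed factor in the model for 24-month change. In the same sentence, name the level of the random month slope and say whether baseline is a response row for WOMAC, so that the role of site is clear.

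The cost is one or two sentences and 7 − 1 = 6 degrees of freedom per time contrast, out of about 210 completers. If sites do not differ in change, practically nothing is lost: simulated power was 79.7% without site and 79.6% with it. No new data or patients are needed, the sample size is unaffected, and the change can be made before unblinding.
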